#### Maintenance of nutritional adequacy

It is well established that cancer and its treatment can have a significant negative impact on a patient’s nutritional status. Participants randomised to the intervention will receive an additional tailored dietetic assessment with the exercise programme to ensure nutritional adequacy is maintained throughout the duration of the intervention. Sessions will focus on ensuring adequate dietary energy (25-30kcals/kg/day) and protein intake (1.25–1.5 g/kg/day). These reference levels are recommended in the ESPEN guidelines for cancer patients [22]. Assessments will be carried out by a registered dietitian with experience working with surgical oncology patients.

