## Methods

### Study aims

The primary aim of this work is to examine the effect of a preoperative high intensity interval training programme on cardiorespiratory fitness in patients scheduled for oesophagectomy and major lung resections.

Secondary aims are;
To examine if individually prescribed preoperative exercise training can reduce postoperative complication rates following thoracic oncological resections.To determine if individually prescribed preoperative exercise training can impact post-operative physical recovery following complex thoracic oncological resections.To determine if individually prescribed preoperative exercise training restores preoperative cardiorespiratory fitness to pre-treatment levels in patients treated with preoperative chemo(radio)therapy and surgical resection.To examine if individually prescribed preoperative exercise training can reduce postoperative healthcare costs, in particular acute hospital costs.To qualitatively explore participant’s experience of preparation for surgery on the PRE-HIIT trial.

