### Study design

PRE-HIIT will be implemented as a randomised controlled trial with two arms: i) an intervention group offered the 2-week HIIT programme in addition to standard care, and ii) a control group receiving standard survivorship care, which involves standard pre-operative advice and a preoperative moderate intensity exercise programme. Figure 1 depicts the flow of participants through the study. The study will take place in the Wellcome Trust-Health Research Board (HRB) Clinical Research Facility (CRF) at St James’s Hospital (SJH), Dublin. Ethical approval has been sought from the Tallaght University Hospital (TUH)/ SJH Ethics Committee. Any amendment to the protocol which may impact on the conduct of the study will be submitted as an amendment for approval to the ethics committees. The study will be performed according to the Declaration of Helsinki. The study is registered with Clinical Trials.Gov (NCT03978325).

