### Sample size calculation

The primary response is the change in VO_2_peak from baseline (T0) to post-intervention (T1). On the basis of estimates calculated from our pilot study, a sample of size 64 (32 in each arm) is needed in order to detect a mean difference in VO_2_peak of 1 ml/kg/min between the control and intervention groups (assuming a standard deviation of change in VO_2_peak of 1.4 ml/kg/min for each arm) with 80% power at the 5% significance level based on a two-sample t-test. Based on the results from the PHIIT trial and others [16, 17], an improvement of 1 ml/kg/min in VO_2_peak is feasible with the exercise intervention prescribed. It is anticipated that the active control group will not experience a change in fitness during this 2 week time period [16]. Moderate intensity exercise interventions have not been shown to significantly change preoperative aerobic capacity and functional capacity of patients due to undergo elective surgery [31].

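### The intervention arm receives HIIT plus tailored dietetic support, but the aims and arm description credit HIIT or exercise training alone

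*Protocol article*

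**What the plan says.** All references are to the protocol article.

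- **Maintenance of nutritional adequacy** (under Intervention): "Participants randomised to the intervention will receive an additional tailored dietetic assessment with the exercise programme". A registered dietitian carries out the assessments, and the sessions work towards stated daily energy and protein intakes. The stated goal is nutritional adequacy during the intervention. Body weight is not named.
- **Standard preoperative care group**: controls receive exercise advice, a moderate intensity exercise programme, the study assessments and health education. No dietetic component is listed.
- **Study design**: the arms are described as "an intervention group offered the 2-week HIIT programme in addition to standard care" against a control group on standard care. Dietetics is not mentioned.
- **Study aims**: the primary aim is to "examine the effect of a preoperative high intensity interval training programme on cardiorespiratory fitness". Four of the five secondary aims (complications, physical recovery, restoration of fitness, healthcare costs) credit individually prescribed exercise training. The Methods and Discussion parts of the abstract use the same exercise-only framing.
- **Table 1**: nutritional status by dietary interview is a secondary outcome at T0 and T1. CPET and anthropometry are also done at both visits.
- **Sample size calculation**: the trial is sized "in order to detect a mean difference in VO_2_peak of 1 ml/kg/min between the control and intervention groups", so the primary target is expressed per kilogram of body weight.

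**The concern.** The arms differ by two components, while the stated aims credit one. A reader of the aims would expect a difference in complications, recovery, quality of life or cost to be evidence about exercise. The nutritional section itself says that cancer and its treatment can seriously impair nutritional status, so dietetic support is a plausible second route to each of these outcomes. For nutritional status the problem is sharper: the dietary interview measures what the dietitian coaches in one arm only, so a between-arm difference there says little about HIIT.

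The primary outcome raises a smaller question. A value in ml/kg/min changes when weight changes, even if oxygen uptake in ml/min does not. Dietetic support and extra exercise could each affect weight, and both are given in one arm only.

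**Working it through.** **1. The contrast, component by component.**

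| Component | Intervention arm | Control arm |
|---|---|---|
| Standard care (advice, moderate intensity programme) | yes | yes |
| Supervised HIIT | yes | no |
| Tailored dietetic sessions | yes | none named |
| Credited in the aims | HIIT or exercise training only | |

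The randomised difference estimates rows two and three together. No feature of the two-arm design separates them.

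**2. The plan's own sample size.** Inputs from the sample size section: difference 1 ml/kg/min, SD of change 1.4 per arm, 80% power, 5% level, two-sample t-test. A two-sided test is assumed, because sidedness is not stated.

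Normal approximation: n per arm = 2 × (1.96 + 0.84)² × 1.4² / 1² ≈ 30.8, so 31. The exact noncentral t gives 79.0% power at 31 per arm and 80.3% at 32. The stated 32 per arm (64 in total) is therefore reproduced. At the 39 per arm to be recruited, power is 87.6%.

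**3. Sensitivity of a per-kilogram value to weight.** Let V be VO2peak in ml/kg/min and W weight in kg. Absolute uptake is V × W. If it stays fixed and the patient loses 1 kg, the per-kilogram value changes by

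V × W / (W − 1) − V = V / (W − 1).

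The document gives neither baseline weight nor baseline VO2peak. Over an assumed 65-80 kg and 16-20 ml/kg/min:

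| | 16 ml/kg/min | 20 ml/kg/min |
|---|---|---|
| 65 kg | 16/64 = 0.25 | 20/64 = 0.31 |
| 80 kg | 16/79 = 0.20 | 20/79 = 0.25 |

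Each 1 kg of between-arm difference in weight change is thus worth about 0.20 to 0.31 ml/kg/min, or 20 to 31% of the 1 ml/kg/min target. The 1 kg is a unit for scaling. The document does not predict how large the difference in weight change will be.

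**4. What that could mean for power.** If a weight effect lowered the observed difference to 0.8 ml/kg/min, power would be 61% at 32 per arm and 70% at 39. At 0.7 it would be 50% and 59%. If the effect ran the other way, the difference would be overstated by the same 0.2 or 0.3. To cancel the whole target, the intervention arm would have to become heavier, relative to control, by a fraction 1/(V − 1): 1/19 = 5.3% at 20 ml/kg/min and 1/15 = 6.7% at 16.

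**The case against.** The strongest reply is that nothing is hidden. The dietetic sessions are described under the Intervention heading, participants are randomised to the PRE-HIIT programme, and testing a package is a legitimate design. The economic evaluation is also largely framed around the programme, and its implementation costs include clinician salaries. All of this stands, and it confines the defect to wording: the aims and arm description name one component of a two-component programme. The word 'additional' also leaves room for some dietetic input in usual care, which would narrow the asymmetry without removing it.

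A supporting analysis in ml/min is the kind of detail usually left to an analysis plan, which is not shown. Its absence is not counted here as a fault. It is offered as cheap support.

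Three stronger readings are tempting, and the document supports none of them.

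- **That the trial cannot attribute its fitness result at all.** Randomisation is intact and the comparison is valid for the package. For VO2peak, the document offers no mechanism by which dietetic sessions over a programme of about two weeks would by themselves produce the targeted gain. The separation problem weighs mainly on the secondary outcomes.
- **That the dietetic support targets the denominator of the primary endpoint.** The text targets energy intake, protein intake and nutritional adequacy. An effect on weight is an inference.
- **That any weight effect biases towards no difference.** This assumes that controls lose weight and the intervention arm does not. The intervention arm also expends extra energy, in sessions up to five days a week, so dietetic support might only offset that loss. The direction is unknown.

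**Conclusion.** The point holds as a mismatch between the stated aims and the randomised contrast. A conclusion about HIIT alone on complications, recovery, quality of life, nutritional status or cost would not follow from this comparison, whereas a conclusion about HIIT with dietetic support would. That part rests on the text alone.

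The weight sensitivity is secondary: 0.20 to 0.31 ml/kg/min per 1 kg of differential weight change, conditional on the assumed baseline ranges and on absolute VO2 staying fixed. Neither the size nor the sign of any such difference can be predicted from the document. The sample size of 64 is correct on its own inputs and is not affected.

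**What to change.** 1. In the abstract, aims and study design, describe the contrast as HIIT plus dietetic support versus standard care, and word the conclusions to match.
2. Make no HIIT-only claim for complications, recovery, quality of life, nutritional status or cost. In the economic comparison, say explicitly that the dietitian's time is part of the programme cost, because the quality of life section names only the cost of the exercise programme.
3. Report dietary intake as a process measure showing delivery of the dietetic component, not as an outcome of HIIT.
4. Alongside the primary result, report weight change by arm and one supporting analysis of VO2peak in ml/min, or with T0 weight as the denominator at both visits.

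The cost is a narrower conclusion, some rewording and one extra analysis. CPET and anthropometry are already scheduled at T0 and T1, so no new visits, patients or changes to care are needed.

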#### Standard preoperative care group

The standard care control group will not be invited to participate in the HIIT exercise group. They will however form an active control group, as standard preoperative care at St James’s Hospital includes standard pre-operative exercise advice and prescription of a moderate intensity exercise programme. Patients will also complete preoperative assessments as described and receive pre-operative health education.

### Measures

PRE-HIIT study outcomes are listed in Table 1. The main assessment battery will be performed at; diagnosis (oesophageal cancer patients scheduled for neoadjuvant treatment) (DX), baseline (T0), and post-intervention (T1). Quality of life will be further assessed at 3 months post intervention. Key timepoints for assessing outcomes of exercise prehabilitation intervention are outlined in Fig. 2. At baseline information regarding socio-demographics will be collected from patient interview and data pertaining to medical history, cancer diagnosis and treatments will be obtained from patient’s medical records.

**Table 1 Tab1:** Pre-HIIT Outcomes

Outcome	Instrument	Diagnosis	Baseline	Post-intervention	Post-Operatively
		Dx	T0	T1	
**Primary outcome**					
Cardiorespiratory fitness	Cardiopulmonary Exercise Test (CPET)	X	X	X	
**Secondary outcomes**					
*Pulmonary and Physical Performance*					
Functional performance	Short Physical Performance Battery (SPPB)	X	X	X	
Muscle Strength	Leg Press 1-RM	X	X	X	
Physical activity	International Physical Activity Questionnaire	X	X	X	
Pulmonary Function	CPET	X	X	X	
Maximum Inspiratory Pressure	PowerBreathe K-series	X	X	X	
Nutritional Status	Dietary interview	X	X	X	
Quality of Life	EORTC-QLQ-C30	X	X	X	X
Cancer specific quality of Life	EORTC-QLQ-OG25 (oesophago-gastric cancer)	X	X	X	X
	EORTC-QLQ-LC 13 (lung cancer)	X	X	X	X
Qualitative approach	Semi –structured interviews (focus groups or 1:1)			X	
Cost analyses	EQ5D				X
	Service Use Inventory				X
**Post-operative morbidity**					
Post-operative outcomes	Self-reported Functional Recovery				X
	Post-Operative Morbidity Score				X
	Clavien Dindo Score				X
	Comprehensive Complications Index				X
**Other**					
Adherence	Record in case report form/ exercise diary			X	
Sociodemographic details	Participant self-report		X		
Body composition	Anthropometry		X	X	
Cancer/Surgery history	Medical records		X		
Adverse events	Reports of patients/ research personnel			X

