### Intervention

#### Preoperative exercise intervention

The exercise intervention will take the form of a supervised programme, completed for at least 2 weeks, up to 5 days per week preoperatively. The feasibility of this protocol has been established by our PHIIT trial, which recruited patients scheduled for thoracotomy and colorectal surgery at St James’s Hospital, with compliance rates of 86% and adherence of 98%. Furthermore, the study design is similar to the format prescribed by the PREPARE trial [20], which specified a minimum study duration (at least 2 weeks) but continued to prehabilitate patients for longer in the lead up to surgery to optimise the benefits gained [21]. The 2-week preoperative timeline was found to be acceptable in the oesophagectomy clinical pathway at our Centre.

The HIIT programme will be performed on an electromagnetically braked cycle ergometer in the exercise physiology room at the CRF in St. James’s Hospital under the supervision of a physiotherapist with experience in exercise prescription and exercise oncology. Exercise sessions will be individually supervised and scheduled at a time of convenience for each participant. Each exercise session will last 40 min and will include warm-up, exercise training and cool-down components. Lactate threshold, measured during the baseline CPET, will be used to determine the exercise intensity.

The intervention will prescribe the same HIIT protocol used by the PHIIT trial, with established safety and feasibility. The training protocol will prescribe 15 s intervals of exercise and passive recovery. The highest resistance reached during the baseline CPET (measured in watts) will be recorded as the peak power output (PPO). During training, participants will undergo a 5-min warm-up at 50% PPO, followed by up to 30 min of HIIT with intervals of 15 s at 100% PPO with 15 s recovery periods at 0 watts. Vital signs including heart rate, blood pressure, perceived exertion, and oxygen saturation levels will be measured throughout. A 3-min cool down will be performed upon session completion followed by a passive recovery period of up to 7 min. Preliminary evidence from both our PHIIT feasibility trial and the published literature [16, 17], supports the hypothesis that this exercise prescription will produce a clinically and significantly meaningful increase in cardiopulmonary fitness.

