### Safety

Prior to baseline testing, all participants will require written medical approval confirming their suitability for participation. Patients will only be formally enrolled on the study after successfully completing a CPET with ECG monitoring. All CPET will be medically supervised and will take place in the CRF which is located within SJH and is covered by the hospital’s emergency response team. All adverse events will be recorded, and serious adverse events will be reported to the research ethics committees.

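### Adverse events have one scheduled point (T1) and no stated common elicitation, while only the HIIT arm is observed between T0 and T1, so by-arm counts of preoperative events would be open to ascertainment bias.

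*Protocol article*

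**What the plan says.** Table 1, in its block of other measures, gives adverse events a single mark in the T1 column. Dx, T0 and the postoperative column are blank. The source is "Reports of patients/ research personnel". The Safety section has no time point and no limit to one arm: "All adverse events will be recorded, and serious adverse events will be reported to the research ethics committees". It also states: "Patients will only be formally enrolled on the study after successfully completing a CPET with ECG monitoring".

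Contact before surgery differs by arm:

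- **HIIT.** The programme is "completed for at least 2 weeks, up to 5 days per week preoperatively". On supervision: "Exercise sessions will be individually supervised and scheduled at a time of convenience for each participant". At those sessions, "Vital signs including heart rate, blood pressure, perceived exertion, and oxygen saturation levels will be measured throughout". There is one more contact: "Participants randomised to the intervention will receive an additional tailored dietetic assessment with the exercise programme".
- **Control.** The section on the standard care group says that "standard preoperative care at St James’s Hospital includes standard pre-operative exercise advice and prescription of a moderate intensity exercise programme". Controls also complete the common preoperative assessments and receive health education. No supervised session and no adverse-event contact between T0 and T1 is described for them.

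**The concern.** The printed schedule is narrower than the safety rule in the same article, so a reader cannot tell when adverse events are collected or from what point.

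The second difficulty is the source. Between T0 and T1, research staff as described can observe events directly in one arm only. A symptom or abnormal reading at a HIIT session is seen as it happens. The same event in a control comes to light only if the patient mentions it or is asked about it later. A count by arm would then mix harm from the programme with intensity of observation. Preoperative tolerability bears directly on whether such a programme is adopted before major resection, so an apparent excess in the HIIT arm would be hard to interpret. A control who has an event and does not return for T1 has no described route for capture before surgery.

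**Working it through.** **1. Is there a figure to reproduce?** No. The article gives no adverse-event rate, detection rate or safety sample size.

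**2. Schedule against rule.** Table 1 has one mark, at T1. The Safety section covers all adverse events, with no time limit. The adherence row of Table 1 also has a single T1 mark, yet the Adherence section describes monitoring during each supervised session. A T1 mark in this table can therefore stand for data accumulated from T0 to T1. On that reading two things remain open: Dx and T0 are still unmarked, although maximal exercise tests take place at both, and the session-by-session source still exists for HIIT only.

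**3. Observation opportunities between T0 and T1.** Maximum sessions = weeks × 5.

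| Programme length | HIIT sessions, maximum | Control contacts described |
|---|---|---|
| 2 weeks | 2 × 5 = 10 | 0 |
| 3 weeks | 3 × 5 = 15 | 0 |
| 4 weeks | 4 × 5 = 20 | 0 |

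Two weeks is a minimum, so 10 is not a ceiling. The 3- and 4-week rows are illustrations.

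**4. What unequal detection could do.** Let p be the true risk per patient, equal in both arms, and d the probability that an event is recorded.

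- Recorded rate = p × d.
- Recorded risk ratio = (p × d_HIIT) / (p × d_control) = d_HIIT / d_control, so p cancels.

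Assumptions, none from the document: d_HIIT = 100%, d_control = 90% to 30%, p = 10% to 40%. The number per arm, 39, is the recruitment target in the Abstract. Expected patients with a recorded event = 39 × p × d.

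| d_control | Ratio (1 / d_control) | p = 10%: HIIT vs control | p = 20%: HIIT vs control | p = 40%: HIIT vs control |
|---|---|---|---|---|
| 90% | 1.11 | 3.9 vs 3.5 | 7.8 vs 7.0 | 15.6 vs 14.0 |
| 70% | 1.43 | 3.9 vs 2.7 | 7.8 vs 5.5 | 15.6 vs 10.9 |
| 50% | 2.00 | 3.9 vs 2.0 | 7.8 vs 3.9 | 15.6 vs 7.8 |
| 30% | 3.33 | 3.9 vs 1.2 | 7.8 vs 2.3 | 15.6 vs 4.7 |

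If HIIT detection is itself incomplete the ratio shrinks in proportion: 90% against 50% gives 0.90 / 0.50 = 1.8. With equal detection it is 1.0.

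**5. Events at the Dx and T0 exercise tests.** Randomisation follows the T0 assessment, so these events cannot create an arm difference. They bear only on completeness. The Recruitment section places written consent at the visit for baseline testing, and the Safety section places formal enrolment after a successfully completed test. A patient whose test ends in an event may therefore have consented without being enrolled, and Table 1 does not say whether that event counts.

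**6. After surgery.** Complications, length of stay and mortality are recorded at discharge and on postoperative day 30, without restriction to one arm. The gap is preoperative.

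**The case against.** The strongest reply is that one table cell is being over-read. The Safety section already promises that every adverse event is recorded, and the adherence row shows that a T1 mark can cover accumulated data. That stands: the documents do not show that events are noted only on the T1 visit day. It does not remove the mismatch at Dx and T0 or the one-sided source between T0 and T1.

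A second reply is that no between-arm comparison is planned. Adverse events are not among the primary or secondary outcomes, and the Statistical analysis section names no test for them. That also stands. A reader might infer that the trial's safety comparison is biased; the documents support only that a by-arm tabulation, if made, would be open to bias.

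Other stronger readings also fail:

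- **That reports are purely spontaneous.** The article does not say whether patients are asked systematically, and research personnel are a named source.
- **That the worst-affected patients are lost.** This is least plausible in the HIIT arm, where staff see patients at sessions and the Adherence section tracks discontinuation, interruption and early termination. Serious events go to the ethics committees, and postoperative harm is captured in both arms. What remains is a control with a preoperative event who misses T1, and even there nothing says that the event goes unrecorded.
- **That exercise-test events distort the contrast.** They precede randomisation.

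Finally, elicitation detail often sits in a full protocol, which is not at hand. Silence on detail alone would be no finding. The point rests on what the article does print: a schedule narrower than its own rule, and a collection source that by design operates unequally between the arms.

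**Conclusion.** The concern holds in limited form. Table 1 and the Safety section need reconciling, and the collection method as stated leaves any by-arm description of preoperative adverse events open to ascertainment bias. The likely direction, against HIIT, follows from the described contact pattern. The size does not: the range of 1.11 to 3.33 rests entirely on assumed control detection of 90% to 30%, full HIIT detection and equal true risk. It also supposes that controls have no research contact beyond what the article describes. Neither a demonstrated bias nor a demonstrated loss of events is shown. The primary outcome is untouched. This is a worthwhile, inexpensive improvement to the safety data.

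**What to change.** - **Table 1 and Safety section.** State in both that adverse events are recorded from consent, including during the Dx and T0 exercise tests and whether or not formal enrolment follows. The purpose is complete safety data, not the arm contrast.
- **Same questions in both arms.** Use one short structured set of adverse-event questions at T1, by telephone if T1 is missed. Someone other than the blinded assessor should ask them, because event descriptions can reveal allocation.
- **Reporting.** Base any between-arm description of preoperative events on those answers. Report signs detected at supervised sessions separately, as descriptive HIIT-arm data.
- **Postoperative period.** Harm is already captured at discharge and on day 30, so a further form at the day 30 call is optional.

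The cost is one short form, a few minutes per patient at an existing visit, and occasional calls to patients who miss T1. Treatment, visits and sample size do not change.
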